#### Nerve conduction studies.

Nerve conduction studies are performed to confirm the presence of a distal symmetrical polyneuropathy, following the recommendations of the American Academy of Neurology and the American Association of Electrodiagnostic Medicine [55]. The initial assessment includes sural sensory and peroneal motor nerve conduction studies in one lower limb. If both results are normal, no further testing is required to exclude large-fibre distal symmetrical polyneuropathy.

If either study is abnormal, additional tests are undertaken as appropriate. These may include assessments of the ipsilateral tibial motor nerve; the contralateral sural sensory, peroneal motor, or tibial motor nerves; or the median sensory and ulnar sensory and motor nerves in one upper limb.

Electrodiagnostic confirmation of a length-dependent distal symmetrical polyneuropathy is defined as an abnormality in any attribute of nerve conduction in at least two separate nerves, one of which must be the sural nerve. Variables such as skin temperature, age, and height are taken into account when interpreting results.

#### Axonal excitability.

In selected cases, axonal excitability will be assessed using an electrophysiological technique known as threshold tracking [23]. Nerve excitability reflects the biophysical properties of myelinated axons and their membrane potential. These measurements complement conventional nerve conduction studies, which primarily assess action potential amplitude and latency but provide limited information about underlying membrane dynamics. In contrast, threshold tracking is sensitive to changes in membrane potential at the site of stimulation.

Key parameters include refractoriness, supernormality, the strength–duration time constant, and threshold electrotonus. Recordings will be obtained from the motor and sensory divisions of the median nerve in accordance with published recommendations [56]. This approach also enables modelling of ion channel function.

#### Quantitative sensory testing.

Quantitative sensory testing is a psychophysical technique used to assess sensory perception in response to defined stimuli. It provides a quantitative measure of sensory function and generates a sensory profile that captures both loss and gain of function across multiple sensory modalities. Quantitative sensory testing will be performed according to a modified version [42] of the German Research Network on Neuropathic Pain (DFNS) protocol [20,57]. In this study population, most participants are expected to experience bilateral symptoms; therefore, testing will be performed unilaterally on the dorsum of the foot and/or hand.

Quantitative sensory testing data will be entered into the Equista software package (version 1.2.2., CASQUAR GmbH), developed by the German Research Network on Neuropathic Pain. Equista converts raw data into z-scores, normalising results for age, sex, and the body region tested [58]. A z-score of zero represents the population mean, while scores greater than +2 or less than –2 standard deviations indicate gain or loss of function, respectively.

Participants will be stratified into somatosensory phenotype groups based on their quantitative sensory testing results. Two complementary approaches will be used:

Cluster analysis – An unbiased algorithm identifies three distinct phenotypic groups: sensory loss, mechanical hyperalgesia, and thermal hyperalgesia. Individuals will be assigned deterministically to one of these groups [13,19].Irritable versus non-irritable phenotype – Participants will be classified as having an irritable phenotype when detection thresholds are normal but there is evidence of sensory gain (mechanical or thermal hyperalgesia), or a non-irritable phenotype when there is either sensory loss or no evidence of sensory gain [59].

#### Skin biopsy.

Intra-epidermal nerve fibre density is a validated measure for assessing small-fibre pathology. Skin biopsy samples will be obtained in accordance with the published guidelines of the European Federation of Neurological Societies/Peripheral Nerve Society on the use of skin biopsy in the diagnosis of peripheral neuropathies [60]. The biopsy will be taken at the end of the clinical assessment, from a site located 10 cm proximal to the lateral malleolus, once all other relevant investigations have been completed.

Participants will not undergo a skin biopsy if they decline the procedure, are receiving warfarin or other anticoagulant therapy, or have contraindications such as local skin infection or ulceration.

#### Genotyping.

This study uses DNA and RNA sequencing to investigate the genetic and molecular mechanisms that drive changes in C-fibre axonal properties and excitability. We will collect blood samples to extract DNA and analyse genetic variants that may influence C-fibre axonal properties and nociceptor excitability, focusing on genes involved in ion channel function and peripheral nerve signalling. We will extract RNA from blood and skin samples to characterise gene expression using high-throughput RNA sequencing, enabling us to identify transcriptional changes that modify C-fibre excitability and sensory transduction. Sequencing data will be processed through validated bioinformatic pipelines, with key findings verified using quantitative methods such as RT-PCR.

Together, these approaches will reveal how genetic and molecular factors shape C-fibre function by identifying variants and expression changes linked to altered axonal behaviour and nociceptor properties.

### Data analysis

#### Patient stratification.

Patient study participant’s neuropathy [61] and pain [1] is graded according to published guidelines. The diagnosis of distal symmetrical polyneuropathy (DSP) is based on a detailed neurological assessment in combination with tests.

**Table pone.0349407.t001:** 

No DSP	No abnormalities on clinical assessment or tests
Subclinical DSP	Abnormal tests but no signs or symptoms
Possible DSP	Symptoms: decreased sensation, positive neuropathic sensory symptoms in the toes, feet, or legs, e.g., numbness, burning; or Signs: symmetric decrease of distal sensation or unequivocally decreased or absent ankle reflexes
Probable DSP	Two or more: neuropathic symptoms, decreased distal sensation, or unequivocally decreased or absent ankle reflexes
Confirmed DSP	Abnormal nerve conduction tests or a measure of small-fibre dysfunction (intraepidermal nerve fibre density or thermal thresholds), and abnormal clinical assessment (a symptom or sign)

Participants are then graded according to the presence or absence of neuropathic pain. Neuropathic pain classification is based on whether the pain present is neuropathic in nature and follows a distinct neuroanatomically plausible distribution.

Participants included in analysis will be divided into groups based on aetiology, neuropathy, and neuropathic pain grading [10].

i. **Diabetic participants** are divided into those with (possible/probable/confirmed) and without a distal symmetrical polyneuropathyii. **Diabetic participants with a distal symmetrical polyneuropathy** are further divided into those with and without neuropathic pain.iii. **Non-diabetic participants** with distal symmetrical polyneuropathy are divided into those with and without neuropathic pain. This will include participants with small-fibre neuropathy, i.e., those participants with injury confined to the small fibres (Aδ and C-fibres.)iv. **Extreme pain phenotypes** include:

**Erythromelalgia** and **paroxysmal extreme pain disorder** – episodic or persistent pain and erythema of the extremities or trunk that is exacerbated by warming and relieved by cooling;

**Familial episodic pain syndrome** – severe episodic pain localised to the trunk and limbs with no structural cause;

**Insensitivity to pain** – inability to feel nociceptive stimuli

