#### Planned primary analysis.

Between-group comparisons (neuropathic pain vs no neuropathic pain) will be conducted using appropriate non-parametric tests (Mann–Whitney U test) where data are not normally distributed, or independent-samples t-tests where normality is satisfied.

Data from individual nociceptive fibres will be analysed with explicit consideration of clustering within participants. Where appropriate, fibre-level measurements will be summarised at the participant level (for example, by averaging) to provide an independent observation per participant for primary analyses. In addition, mixed-effects models will be used, with participant included as a random effect, to account for within-participant variability. Multiplicity arising from multiple outcomes will be addressed using appropriate multiple-comparison adjustments (for example, Bonferroni or false discovery rate correction).

This dual approach allows us to perform conservative primary analyses at the participant level by averaging, while also utilising more sophisticated modelling through a mixed-effects model that retains the detail of the individual fibre data while correcting for the dependence between fibres from the same participant. The mixed-effects model will bridge the participant (unit of inference) and individual fibre (unit of observation) without the statistical error of treating fibres from the same person as independent data points.

Multivariable logistic regression models will be used to examine the association between neuropathic pain status and microneurography-derived measures of axonal excitability and properties, adjusting for prespecified covariates (age, sex, diabetes status, neuropathy severity, and medication use).

Multicollinearity among predictors will be evaluated using variance inflation factors; when two predictors are highly correlated, the variable with greater variance or stronger biological relevance will be retained in the final model.

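### A painful symptom alone can decide whether a diabetic participant is graded as having DSP, so entry to the painful versus painless DSP groups depends partly on pain itself

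*Protocol article*

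**What the plan says.** The rule is in the Protocol article, Data analysis, Patient stratification, and the grading table that follows it.

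- No DSP: "No abnormalities on clinical assessment or tests".
- Subclinical DSP: "Abnormal tests but no signs or symptoms".
- Possible DSP: symptoms or signs, no test required: "positive neuropathic sensory symptoms in the toes, feet, or legs, e.g., numbness, burning; or Signs".
- Probable DSP: at least two of neuropathic symptoms, decreased distal sensation, and reduced or absent ankle reflexes.
- Confirmed DSP: an abnormal nerve conduction or small-fibre test "and abnormal clinical assessment (a symptom or sign").

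Below the table, diabetic participants are sorted into those with DSP (the possible, probable and confirmed grades) and those without. Those with DSP "are further divided into those with and without neuropathic pain". Non-diabetic participants with DSP are split by pain in the same way, but the qualifying grades are not restated for them.

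On pain: "Neuropathic pain classification is based on whether the pain present is neuropathic in nature and follows a distinct neuroanatomically plausible distribution". That sentence names no confirming sign or test. The text introducing the table says that the DSP diagnosis "is based on a detailed neurological assessment in combination with tests".

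Under Planned primary analysis, the contrast is neuropathic pain versus no neuropathic pain, and the logistic models are described as "adjusting for prespecified covariates (age, sex, diabetes status, neuropathy severity, and medication use").

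**The concern.** A grading of diagnostic certainty may reasonably count symptoms. The same grading causes trouble when it sets who is eligible for a comparison of painful with painless neuropathy, because the symptom that admits a participant can be the pain that then assigns the group. People with identical signs and test results are treated differently according to whether they hurt.

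If so, restricting a comparison to people with DSP does not make the two groups alike in nerve damage. The painful group can include people with no objective abnormality. The painless group cannot include their counterparts, nor people whose only finding is an abnormal test. A difference in C-fibre measures between the groups, or the lack of one, could then partly reflect the definition.

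**Working it through.** No stated figure is contested, so there is none to reproduce. The check applies the grading rule to every combination of findings.

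**Inputs** (all from the grading table): five yes/no findings, namely a painful symptom such as burning, a non-painful symptom such as numbness, decreased distal sensation, reduced or absent ankle reflexes, and an abnormal test. This gives 2^5 = 32 combinations, or 2^4 = 16 patterns of the other four findings, each taken with and without the painful symptom. A participant is in the DSP group if graded possible, probable or confirmed.

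**Result.**

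| Other four findings | Without painful symptom | With painful symptom | Does pain alone change entry? |
|---|---|---|---|
| Nothing abnormal (1 pattern) | No DSP: not listed as DSP | Possible: in | Yes |
| Abnormal test only (1 pattern) | Subclinical: not listed as DSP | Confirmed: in | Yes |
| Numbness or at least one sign, with or without an abnormal test (14 patterns) | Possible, probable or confirmed: in | In | No |

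The last row has (2^3 − 1) × 2 = 14 patterns: at least one of the three clinical findings, times test normal or abnormal. Pain alone therefore decides entry in 16 − 14 = 2 patterns. These are counts of patterns, not of participants; the documents do not say how common each is.

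**Consistency with the introductory sentence.** The diagnosis is said to rest on assessment together with tests, yet the Possible grade requires no test and counts as DSP for diabetic participants. The two statements do not fit well.

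**Illustration of size, on assumptions not in the documents.** Suppose a share f of the painful group entered on burning alone and carries none of a true standardised difference d, with the SD unchanged. The observed difference is then d(1 − f). Take d = 0.5, a value the article gives only for its quantitative sensory testing (QST) cluster analyses, with 64 per group and two-sided α = 0.05. Power = Φ(d(1 − f)√(64/2) − 1.96).

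| f | d(1 − f) | Power |
|---|---|---|
| 0 | 0.50 | 81% |
| 0.1 | 0.45 | 72% |
| 0.2 | 0.40 | 62% |
| 0.3 | 0.35 | 51% |

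This shows only how such dilution would behave if it occurred.

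**The case against.** Several points on the other side stand, and they limit the finding.

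- **The primary contrast.** A reader might infer that the main comparison is biased. The Statistical plan and Planned primary analysis sections do not restrict it to DSP, so No DSP and Subclinical participants can serve there as no-pain participants.
- **Abnormal tests without symptoms.** A reader might infer that these count as no DSP. An abnormal test plus a sign, with no symptom, is Confirmed. Only an abnormal test with neither is Subclinical, which has its own row, and the No DSP row excludes abnormal tests. That Subclinical falls on the without-DSP side is implied by the two-way diabetic split and stated nowhere.
- **Other routes in.** Numbness alone also gives Possible DSP, so symptom-only participants can enter the painless group too. The dilution illustration ignores this.
- **Direction.** It is tempting to say that the bias runs towards the null, or makes painful fibres look healthier. The documents do not support this. The Introduction says that ion-channel changes can cause hyperexcitability and that conventional conduction studies cannot assess C-fibres, so burning with normal tests does not imply normal C-fibres.
- **The severity covariate.** If the grade were used, two of its levels would exclude symptoms, and pain status would be partly built into the covariate. The article does not say that it is used. Clinical neurological assessment offers the Toronto score. Sample size justification allots 8 degrees of freedom: age, sex and diabetes take 3, medication at least 3, and a five-level grade would take 4, giving at least 10. A grade scored linearly would fit, so the circularity is possible but not shown.
- **Published grading.** Neuropathy and pain are graded by cited guidelines that are not shown, and the pain grading may screen out some burning-only cases. This does not reach the second pattern in the same way, since an abnormal test is present there.

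None of this removes the asymmetry: under the printed rule, the painless counterparts of the two patterns are outside the grades listed as DSP.

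**Conclusion.** The point holds for the diabetic groups of DSP with and without neuropathic pain. Under the stated rule, a painful symptom alone moves a participant into DSP in 2 of 16 patterns, and the groups can therefore differ in objective nerve damage by construction. It extends to the non-diabetic groups only if the same grades qualify there, which is not stated. It reaches the primary contrast only if that contrast is restricted to DSP.

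The size and direction of any bias are not known from the documents; the powers of 72%, 62% and 51% rest entirely on assumed values of f and a borrowed d. The conclusion also assumes that burning in a plausible distribution can be classified as neuropathic pain without a confirming sign or test, as the printed sentence allows. The finding supports a parallel analysis and clearer group definitions. It does not support abandoning the published grading or moving Subclinical cases into the painless DSP group.

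**What to change.** 1. For painful versus painless DSP comparisons, prespecify an analysis in which DSP membership requires at least one non-symptom criterion: decreased distal sensation, reduced or absent ankle reflexes, or abnormal nerve conduction, intraepidermal nerve fibre density or thermal thresholds. Report it beside the analysis that uses the published grades.
2. In that analysis, hold Subclinical DSP as its own explicit group, so that it is not absorbed into the without-DSP group.
3. State which grades qualify as DSP for non-diabetic participants, and reconcile the introductory sentence on tests with the counting of Possible as DSP.
4. Say how the neuropathy severity covariate is measured, and choose a measure that does not count painful symptoms.

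The cost is wording and one further analysis; the items are already in the assessment plan. The analysis set will be slightly smaller because symptom-only participants leave it. Nerve fibre density will be missing for those without a biopsy (refusal, anticoagulation, local skin contraindication), so the sign-or-test criterion will rest on less information for some participants, and their number should be reported.

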#### *Characterisation of pain – pain location, intensity, quality, analgesics*.

We assess the presence and duration of pain, including dysaesthesia. Participants are asked to indicate where they feel pain on their body using a list of body sites and a body map. They identify all areas where they have experienced pain over the past three months and mark the location that bothers them the most.

Pain intensity is measured using different scoring systems such as the Chronic Pain Grade [43] over the past three months and the Brief Pain Inventory [44]. An additional item asks about the average pain experienced over the past seven days. Pain descriptors are characterised by the DN4 (*Douleur Neuropathique en 4 questions*) [45], and the Neuropathic Pain Symptom Inventory [46]. These questionnaires use an 11-point numerical scale to quantify severity of pain and symptoms.

The Michigan Neuropathy Screening Instrument is a screening tool for diabetic neuropathy and asks participants about symptoms related to diabetic neuropathy, such as pain, numbness, tingling, and loss of sensation in the feet and legs [47].

We record details of pain medication (e.g., paracetamol, gabapentin), dose, analgesic relief, and adherence to medication.

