### Specialised investigations

#### Microneurography.

Microneurography records single-unit activity from peripheral sensory nerves in awake participants by inserting a microelectrode into a peripheral nerve [54]. We typically use the superficial peroneal nerve on the dorsum of the foot because it is superficial, purely sensory, anatomically relevant to distal symmetrical polyneuropathy, and generally well tolerated. It is also the most distal nerve available, which provides an advantage for length-dependent (‘dying-back’) neuropathies that show a distal-to-proximal gradient. In older participants (>70 years) or those with severe neuropathy where the superficial peroneal nerve is denervated or inaccessible, alternative sites (superficial radial nerve or more proximal peroneal sites) will be used.

C-fibres are characterised by the phenomenon of activity-dependent slowing of conduction velocity in response to repetitive transcutaneous electrical stimuli, and natural stimulation in a series of experiments [24].

The core protocol will consist of:

Identification of C-fibres at 0.25 Hz stimulation. After identification, stimulation is paused for three minutes to allow baseline recovery, followed by six minutes at 0.25 Hz. The rate is then increased to 2 Hz for three minutes and followed by a further six minutes at 0.25 Hz. The pause and 0.25 Hz blocks may be adjusted for participant tolerability, but the 2 Hz block will not be shortened.

Where possible this will be followed by the extended protocol.

Stimulation at 0.125 Hz, 0.25 Hz, 0.5 Hz and 1 Hz for at least two minutes at each frequency.Paired-pulse testing to assess recovery cycles by delivering a test stimulus at progressively shorter intervals after a conditioning stimulus.Mechanical and thermal natural stimulation of the receptive field using von Frey hairs and thermal probes (40°C, 45°C, 48°C and 20°C) to determine transduction thresholds and sensitisation to mechanical and thermal stimulation.

We aim to record from up to three independent receptive fields per participant, but a single stable recording suffices for inclusion. All C-fibres will undergo the core protocol; the extended protocol is optional and recorded whenever feasible.

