#### Statistical plan.

Analyses will address the relationships between neuropathy, neuropathic pain, quantitative sensory phenotype and microneurography measures of nociceptor excitability and axonal properties. Analyses will be prespecified, scripted for reproducibility and conducted using appropriate statistical software.

Continuous variables will be summarised using mean (standard deviation) or median (interquartile range) depending on distribution; categorical variables will be summarised using counts and percentages. Point estimators will be reported alongside their respective 95% confidence interval. All hypothesis tests will be two-tailed. Where multiple comparisons are performed, p-values will be adjusted using methods appropriate to the comparison (for example Bonferroni or false discovery rate), and this will be reported alongside unadjusted p-values.

The primary hypothesis is that participants with neuropathic pain will exhibit altered axonal properties and excitability compared to those without neuropathic pain. The primary outcome will therefore be a comparison of microneurography measures of axonal excitability and axonal properties between participants with and without neuropathic pain.

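### Neuropathic pain status is a whole-person label not tied to the recorded nerve territory, so the primary contrast may be attenuated or confounded by recording site in participants recorded outside their painful area

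*Protocol article*

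**What the plan says.** All references are to the Protocol article.

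- **Data analysis, Patient stratification.** Pain is graded per person: "Participants are then graded according to the presence or absence of neuropathic pain". The rule is: "Neuropathic pain classification is based on whether the pain present is neuropathic in nature and follows a distinct neuroanatomically plausible distribution". It does not mention the nerve or skin that is recorded.
- **Statistical plan.** The primary outcome is a "comparison of microneurography measures of axonal excitability and axonal properties between participants with and without neuropathic pain".
- **Planned primary analysis.** Fibre values may be averaged per participant and compared by t-test or Mann–Whitney test. A mixed model with participant as random effect is added. The logistic models adjust for age, sex, diabetes status, neuropathy severity and medication use.
- **Microneurography.** "We typically use the superficial peroneal nerve on the dorsum of the foot", chosen partly because it is relevant to distal symmetrical polyneuropathy. Where that nerve is denervated or inaccessible in participants over 70 or with severe neuropathy, "alternative sites (superficial radial nerve or more proximal peroneal sites) will be used". The same section describes a gradient of damage from distal to proximal. Up to three receptive fields are sought, and one stable recording is enough for inclusion.
- **Questionnaires, Characterisation of pain.** Participants mark where they have pain "using a list of body sites and a body map". No stated grouping or analysis uses this.

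**The concern.** The exposure is defined for the whole body and the outcome for a patch of skin. Nothing links the two. A participant with painful feet whose foot nerve cannot be used may be recorded at the superficial radial nerve. If the hand is painless, those fibres still enter the neuropathic pain group. Averaging can also pool fields inside and outside the painful area in one person.

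Two things are at stake.

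- **Attenuation.** If the abnormality is local to painful skin, off-area recordings pull the contrast toward zero. A null result could then not be told apart from recording away from the pain.
- **Confounding by site.** Site changes with age and neuropathy severity, and the protocol itself describes a gradient along the limb. If the groups differ in their mix of sites, the contrast can move either way. Adjusting for age and severity covers this only in part, and the t-test or Mann–Whitney comparison does not adjust for them at all.

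**Working it through.** **1. The plan's own figure.** The Sample size justification gives no power figure for the pain contrast. The nearest statement is for the sensory-testing cluster analyses: d of about 0.5, 130 diabetic and 148 non-diabetic participants, about 80% power at α = 0.05. A two-sample t-test at d = 0.5 with equal groups needs 64 per group, 128 in total. That is close to 130 (power 80.8%). At 148 the same test has 85.6%. These figures do not test the present point; they only supply a d to borrow.

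**2. Recorded participants.** The target is 124 diabetic and 148 non-diabetic, with minimum recording success of 60% and 80%:

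124 × 0.6 + 148 × 0.8 = 74.4 + 118.4 = 192.8, taken as 96 per group. The even split is an assumption.

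**3. Attenuation.** Let f be the share of the pain group recorded outside the painful area (not in the documents). Let k be the fraction of the abnormality that those off-area fibres still carry. Then

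d_obs = 0.5 × [1 − f(1 − k)]

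power ≈ Φ(d_obs × √(96/2) − 1.96), two-sided 0.05, √48 = 6.928.

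With k = 0, the worst case for attenuation within this model:

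| f | d_obs | d_obs × 6.928 − 1.96 | Power |
|---|---|---|---|
| 0 | 0.50 | 1.504 | 93% |
| 0.1 | 0.45 | 1.158 | 88% |
| 0.2 | 0.40 | 0.811 | 79% |
| 0.3 | 0.35 | 0.465 | 68% |
| 0.4 | 0.30 | 0.118 | 55% |
| 0.5 | 0.25 | −0.228 | 41% |

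Adding the mixture variance f(1 − f) × 0.25 to the pain group, and using a t-test with 97 and 96 participants, gives 93, 87, 78, 67 and 53% for f = 0 to 0.4. The simplification costs at most about two points.

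The result depends on k. With k = 1 there is no attenuation at any f. With f = 0.2 and k = 0.5, d_obs = 0.5 × (1 − 0.1) = 0.45, the same as f = 0.1 with k = 0.

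**4. Site effect.** Let s be the standardised shift in a measure between an alternative site and the foot, and p1 and p0 the shares recorded at alternative sites in the pain and no-pain groups. To first order,

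observed difference = d_obs + s(p1 − p0).

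The documents give neither the sign of s for each measure nor the sign of p1 − p0. The second term can therefore add to the first or subtract from it.

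**The case against.** **The label fits the stated question.** The hypothesis is about participants with and without neuropathic pain, and the participant is named as the unit of inference. A person-level exposure is consistent with that. This stands, and it is why the primary contrast should not be redefined.

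**There is partial matching by design.** The foot is the default site, and the symptoms listed for distal symmetrical polyneuropathy are in the toes, feet or legs. A more proximal electrode does not by itself mean that the receptive field is painless. This stands too: mismatch is probably confined to a minority.

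**The extreme pain phenotypes are weak support.** A reader might infer that familial episodic pain, described as "severe episodic pain localised to the trunk and limbs with no structural cause", puts people with trunk pain and foot recordings into the pain arm. The text says trunk and limbs. These phenotypes form a separate group that is not divided by pain status, and nothing says that they enter the primary pain arm. In inherited channel disorders, fibres away from the pain may also be abnormal.

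**Such detail may belong in the analysis plan.** Risk of bias and mitigation promises a published statistical analysis plan, which is not shown, and it may define site variables. But the article itself fixes the grading rule, the contrast and the covariate list, and the gap lies in how these fit together.

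**Conclusion.** The point holds in limited form. As written, pain status is not tied to the recorded territory, alternative sites are allowed in a subset defined by age or severity, and no stated analysis uses pain location. For participants recorded outside their painful area, the primary contrast may be attenuated or confounded by site in either direction.

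The size is unknown. The power table is a sensitivity range, not a forecast. It rests on an unanchored f, on d = 0.5 borrowed from the sensory-testing analyses, on an even split, on k = 0, and on α = 0.05 without the planned multiplicity adjustment.

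A reader might infer that the primary contrast is in fact diluted toward zero, or that the study is underpowered for this reason. The documents support neither reading: they do not say that off-area fibres behave like no-pain fibres, and they do not say how many such recordings there will be. This is a worthwhile, low-cost improvement to the analysis, not a flaw that invalidates the design.

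**What to change.** Keep the participant-level contrast as primary. For each recording, use the body map and site list already collected to derive whether the receptive field lies inside the participant's painful area. Then prespecify:

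- **(a)** the planned mixed model with pain status at three levels (no neuropathic pain; pain, recorded inside the painful area; pain, recorded outside it), together with recording site as a fixed effect and participant as random effect;
- **(b)** a sensitivity analysis of in-area pain recordings against no-pain recordings at the same nerve site;
- **(c)** a report of the number of pain participants and recordings in and out of the painful area, which supplies the missing f.

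Restricting the primary pain arm to in-area recordings is not advised. It would leave a mostly-foot pain group against a mixed-site comparator and would drop older and more severely affected pain participants selectively.

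The cost is one derived variable and one extra model level. A body map is coarse relative to a receptive field, so some recordings will be misclassified, and the sensitivity analysis will have fewer participants. Recruitment and data collection run to September 2029, so this can still be fixed before the analysis.
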